### 3.4.3 Clinical Experience

PEP3-KLH has been evaluated in a single institution Phase I (VICTORI) and a randomized, multi-institutional Phase II study (ACTIVATE) (Heimberger, Hussain et al. 2006). These studies have demonstrated that vaccinations with an EGFRvIII-specific peptide **induce T- and B-cell immunity**, produce **complete radiographic responses in all patients** with residual tumor (Fig. 3), universally **eliminate EGFRvIII-expressing cells (See Appendices)**(Heimberger, Hussain et al. 2006; Heimberger, Hussain et al. 2006), and **extend median survival to >29 months**(Heimberger, Hussain et al. 2006; Heimberger, Hussain et al. 2006) (Fig. 4) which compares favorably with recently published trials evaluating newly-diagnosed patients with GBM treated with GLIADEL® (13.9 months)(Westphal, Hilt et al. 2003); radiation and concurrent TMZ (14.6 months)(Stupp, Mason et al. 2005); or radiolabeled anti-tenascin monoclonal antibodies performed at Duke University (18.3 months)(Boskovitz, Wikstrand et al. 2004).

[figure not shown]

In the ACTIVATE Trial 23 patients with newly-diagnosed, EGFRvIII-expressing

[figure not shown]

**Fig. 5 Survival of patients treated with PEPvIII vaccine.** Vaccine patients have a median survival of >126 weeks. This compares favorably to carmustine wafers (60 weeks)(Westphal, Hilt et al. 2003) and TMZ (63 weeks)(Stupp, Mason et al. 2005). Median time to progression (TTP) in the multi-institutional ACTIVATE trial was 64 weeks which compared favorably to a matched historical cohort (28 weeks).

GBM who had received gross-total resection followed by conformal radiation with concurrent temozolomide (75mg/m^2/day) without tumor progression, were enrolled. PEP3-KLH (500 mcg/immunization), mixed with GM-CSF (approx. 142 mcg/immunization), were administered intradermally. Nineteen (19) patients received PEP3-KLH at two-week intervals for three (3) doses, while four (4) patients received saline in a blinded fashion for these first three vaccinations. Thereafter, all patients received monthly PEP3-KLH injections until tumor progression.

Toxicity was essentially limited to local reactions and no evidence of induced autoimmunity was reported. All patients experienced mild injection

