### **3.15.1 Dose, Route of Administration, and Dosing Regimen**

This trial is designed to replicate the positive Phase II clinical trial utilizing 500 µg PEP3-KLH with approximately 150 µg GM-CSF as an intradermal injection, given every two weeks for three (3) doses and monthly thereafter.

The initial rationale for dose selection for the Phase II PEP3-KLH study was based on administered doses of peptide in previous trials, which had been as low as 1 µg or as high as 3 mg (Miyagi, Imai et al. 2001). The majority of these clinical trials escalated the dose from 100 mcg to 1 mg without dose-related toxicity or clinical activity. As well, in a previous trial, PEP3-KLH had been administered loaded onto dendritic cells at doses ranging from 150 mcg to 500 mcg, with no reported toxicities (unpublished data).

Further refinement of the dosing is not currently feasible. With agents currently approved for oncologic indications, dosing was defined by either acute toxicity or some immediate biologic readout. There are no reliable short term endpoints to use to select the optimal dose for CDX-110. Local reactions and immune responses are highly variable and have not been shown to correlate with any clinical endpoint. Progression-free survival and overall survival require prolonged follow up and large patient numbers for validity. Thus, the submitted phase II/III trial will be based upon the previously tested dose.

Administration routes for previous peptide vaccine trials have been either intramuscular, intradermal or subcutaneous. No definitive randomized clinical trial has thus far been performed to determine whether one route is preferable over another. However, since the intradermal compartment contains a high concentration of dendritic cells it is thought to be a good vaccination route. As with dose, further refinement of the administration route is not currently feasible. There are no reliable short term endpoints to use to select the optimal route for CDX-110 administration. Thus, the submitted phase II/III trial will use the previously tested route to administer the drug.

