### **5.2 Treatment Procedures**

#### **5.2.1 Vaccination**

After initial leukapheresis, all patients will then receive RT and concurrent TMZ at a standard targeted dose of 75 mg/m^2/d. Patients with progressive disease during radiation, dependent on steroid supplements above physiologic levels at time of vaccination, unable to tolerate TMZ or whose PBLs fail to meet release criteria will be replaced, but no more than 40 patients will be enrolled overall. Remaining patients will then receive the initial cycle of TMZ at a targeted dose of 100mg/m^2/d for 21 days 3 ± 1 weeks after completing RT and will be independently randomized to receive daclizumab versus saline simultaneous with vaccine #1. An additional cohort of 6 patients (cohort #2) will receive serial administrations of daclizumab during vaccine # 1, vaccine # 3, and during the recovery from each TMZ cycle for first 3 cycles at the same dose. Vaccine #1 will be given on day 21 ± 2 days after the start of the 100mg/m^2/d dose of TMZ. Each immunization will be divided equally to both inguinal regions. A total volume of 200 µL

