per side will be delivered intradermally (SOP-JHS-HDC-CL-012 “Administration of Vaccine”). Details of the procedure will be recorded on the appropriate form (FORM-JHS-HDC-CL-012). Injection will be performed using a 1.5 inch 25 gauge needle. Due to the potential for particulates, CDX-110 final drug product should be filtered through a 5 micron filter needle (e.g., Becton Dickinson part no. 305200) prior to administration. The CDX-110/GM-CSF admixture should be injected as soon as possible after mixing. Prior to administration, 0.35 mL of GM-CSF will be withdrawn, under aseptic conditions, from the stock vial of Leukine® (500 mcg/mL) using a hypodermic needle and syringe. This 0.35 mL volume, containing 175 mcg GM-CSF, will be added aseptically to the vial containing 0.6 mL CDX-110, and mixed by gentle inversion of the vial (DO NOT SHAKE). After mixing, 0.8 mL of the CDX-110/GM-CSF admixture will be gently withdrawn (avoiding foaming and excess shearing) *using the provided filtration needle*, under aseptic conditions. The filtration needle should be removed and replaced with an appropriate needle for intradermal injection *before* the injection is administered to the patient. This 0.8 mL dose will contain approximately 500 mcg CDX-110 and 150 mcg GMCSF. Any remaining GM-CSF may be stored for up to 20 days at 2-8°C once the vial has been entered, and utilized for subsequent study drug administrations. Any remaining solution should be discarded after 20 days.

Patients will be monitored in the clinic for thirty minutes to one hour post-immunization for the development of any adverse effects. The immunization procedures will be supervised by a nurse or physician that has completed an Advanced Cardiac Life Support (ACLS) course. A cardiac resuscitation cart will be available in the immediate vicinity when performing these immunizations in case of severe allergic reactions. The initial three vaccines will be given each  $2 \pm 1$  week apart.

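### Section 5.2.1 gives two incompatible vaccine volumes (0.4 mL injected, 0.8 mL called the dose), and Section 9.2.4 gives a third

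*Protocol*

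**What the plan says.** Section 5.2.1 states how each vaccine is injected: "Each immunization will be divided equally to both inguinal regions. A total volume of 200" µL "per side will be delivered intradermally". The reference to SOP-JHS-HDC-CL-012 stands in that same sentence.

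The section then describes preparation. GM-CSF is taken from a 500 mcg/mL stock vial, and "This 0.35 mL volume, containing 175 mcg GM-CSF, will be added aseptically to the vial containing 0.6 mL CDX-110". Next, "After mixing, 0.8 mL of the CDX-110/GM-CSF admixture will be gently withdrawn". The content is then stated: "This 0.8 mL dose will contain approximately 500 mcg CDX-110 and 150 mcg GMCSF".

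Two other sections bear on the intended dose:

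- Section 3.15.1: "This trial is designed to replicate the positive Phase II clinical trial utilizing 500" µg of the peptide conjugate, with approximately 150 µg GM-CSF.
- Section 3.4.3, on the earlier Phase II study: "PEP3-KLH (500 mcg/immunization), mixed with GM-CSF (approx. 142 mcg/immunization), were administered intradermally".

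Section 9.2.4, on infection risk, describes the injected volume as 1 mL spread over more than two intradermal locations.

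On temozolomide, Sections 5.1.1, 5.1.3 and 5.2.1 give a 21-day schedule at 100 mg/m²/d as the recommended default, and the synopsis gives 21 days for the initial cycle. Four places still carry a 5-day schedule: both temozolomide rows of the Section 11 flow sheet, the synopsis sentence on later cycles, and the antiemetic sentence in Section 5.1.3.

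**The concern.** The volume per side is an operative dosing instruction for the investigational vaccine, used at every vaccination. It does not agree with the dose stated a few lines later, and nothing in the protocol reconciles the two. Staff who follow the per-side volume would inject half of what they had just drawn up.

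What is at stake is whether the trial delivers the regimen it says it replicates. If all staff used the smaller volume, both arms would receive half the earlier Phase II dose of CDX-110. If some followed one sentence and some the other, vaccine dose would vary between patients in a randomised cohort of 20, with 10 per arm, and add noise to the immune-response comparisons.

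The temozolomide discrepancy is a separate and smaller matter. The primary objective concerns regulatory T-cell recovery after temozolomide-induced lymphopenia, so the interval from the last temozolomide dose to vaccine #1 and the randomised infusion should be stated in one way only.

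**Working it through.** **Inputs (Section 5.2.1 unless noted).** Two sides; 200 µL per side; 0.35 mL GM-CSF at 500 mcg/mL; 0.6 mL CDX-110 in the vial; 0.8 mL withdrawn; about 500 mcg CDX-110 and 150 mcg GM-CSF in that 0.8 mL. Earlier Phase II GM-CSF dose: about 142 mcg (Section 3.4.3).

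**Step 1: reproduce the stated dose.**
- Admixture volume: 0.60 + 0.35 = 0.95 mL.
- GM-CSF added: 0.35 × 500 = 175 mcg, as stated.
- GM-CSF in 0.8 mL: 175 × 0.8 / 0.95 = 147.4 mcg, which agrees with the stated 150 mcg.
- CDX-110 concentration in the admixture: 500 / 0.8 = 625 mcg/mL, which implies 625 × 0.95 = 594 mcg in the vial, or 594 / 0.6 = about 0.99 mg/mL. The protocol's dosing text does not give the vial strength, so the 500 mcg is taken from the protocol, not verified.

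The preparation step is therefore internally consistent and agrees with Section 3.15.1.

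**Step 2: the volume actually ordered for injection.**
- 2 × 0.200 = 0.400 mL, against 0.8 mL. The ratio is 0.5.

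**Step 3: content of each volume.**

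| Volume | CDX-110 | GM-CSF | Share of the 0.95 mL admixture |
|---|---|---|---|
| 0.8 mL (stated dose) | 500 mcg | 147 mcg | 0.8 / 0.95 = 84% |
| 0.4 mL (200 µL × 2) | 625 × 0.4 = 250 mcg | 175 × 0.4 / 0.95 = 74 mcg | 0.4 / 0.95 = 42% |

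Against the earlier Phase II dose, 74 mcg GM-CSF is 73.7 / 142 = 52%.

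**Step 4: the third volume.** The 1 mL in Section 9.2.4 matches neither figure, and it exceeds the 0.95 mL that the mixing step produces.

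**Step 5: the volume that reconciles 5.2.1.** 0.8 mL / 2 = 400 µL per side.

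**Step 6: temozolomide timing (separate).** Vaccine #1 and the randomised infusion fall on day 21 ± 2 of the initial cycle, that is, day 19 to 23.
- Last temozolomide dose on day 5 (flow-sheet row for the initial cycle): 19 − 5 = 14 to 23 − 5 = 18 days later.
- Last dose on day 21 (synopsis, 5.1.1 and 5.2.1 for this cycle): 19 − 21 = −2 to 23 − 21 = +2 days, so within 2 days either way.

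Only the flow-sheet row for the initial cycle changes this interval. The other flow-sheet row and the synopsis sentence describe later cycles, and the remark in 5.1.3 concerns antiemetics.

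**The case against.** The strongest reply is that the dose itself is never in doubt. Every mass figure for this trial's vaccine agrees, the mixing arithmetic reproduces it, and staff are told that the 0.8 mL is the dose and that each immunization is split equally between two sides. On that view the 200 µL is a slip that no one would act on, and administration follows an SOP in any case.

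Part of this stands. The intended dose can be recovered, and the 200 µL is very probably the error. But the sentence gives 200 µL as the total for each side, so it cannot be read as one of several injections on that side. The text on keeping or discarding leftovers concerns the GM-CSF stock, not half of a drawn-up dose. The SOP is cited in the very sentence that states 200 µL, so it cannot be presumed to correct it.

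A reader might infer more than the protocol supports:

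- **That patients would in fact receive half doses.** This is not established; the SOP and its form are not shown.
- **That the daclizumab comparison is biased.** It is not: both arms get the same vaccine under the same instruction.
- **That 250 mcg would be inactive.** Nothing supports this. Section 3.15.1 says of earlier peptide vaccine trials: "The majority of these clinical trials escalated the dose from 100 mcg to 1 mg without dose-related toxicity or clinical activity".
- **That all four 5-day temozolomide remnants shift the randomised infusion.** Only one does. The 21-day default is readable from the text, and the neuro-oncologist may depart from it.

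**Conclusion.** The point holds and should be fixed. Section 5.2.1 orders 0.4 mL in one sentence and 0.8 mL in another, a factor of two, and Section 9.2.4 adds an incompatible 1 mL. Only 0.8 mL fits the preparation step and the regimen the trial is meant to replicate. Literal use of the per-side volume would give about 250 mcg CDX-110 and 74 mcg GM-CSF instead of about 500 and 147 mcg, in both arms alike.

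The consequence is a possible failure to deliver the earlier regimen, with extra between-patient variability only if staff follow different sentences. It is not a bias in the randomised contrast.

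The figures assume a uniform admixture and accept the stated 500 mcg in 0.8 mL. The temozolomide inconsistency is minor, separate, and adds no weight to this conclusion.

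**What to change.** In Section 5.2.1, change the instruction to 400 µL per side, 0.8 mL in total, and say whether each side's volume is to be spread over more than one intradermal site. In Section 9.2.4, correct 1 mL to 0.8 mL and make the number of locations agree with 5.2.1. Check that SOP-JHS-HDC-CL-012 and its recording form carry the same volume. If 0.4 mL was really intended, restate the dose as about 250 mcg CDX-110 and 74 mcg GM-CSF and amend Section 3.15.1 to match.

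Separately, change the flow-sheet row for the initial temozolomide cycle from days 1-5 to the 21-day default. For consistency, align the later-cycle flow-sheet row, the synopsis sentence on later cycles and the antiemetic sentence in Section 5.1.3.

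The cost is one clarifying amendment and a check of one SOP and its form, with no added procedures or patients.

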### **5.2.2 Daclizumab**

All patients that will receive daclizumab will get it at a 1 mg/Kg dose mixed with 50 mL of sterile 0.9% sodium chloride solution with vaccine #1. A second cohort of 6

---

 ACLS, advanced cardiac life support

patients (cohort #2) will receive serial administrations of daclizumab at vaccine # 1, # 3, and during the recovery from each TMZ cycle for first 3 cycles at the same dose.

### **5.2.3 DTH Placement and Biopsy Procedure**

After completing RT and along with vaccination #1 patients will undergo baseline DTH testing with standard recall antigens. The vaccine site will also be assessed for a DTH-type response. Recall antigens (Tetanus toxoid, *Candida*, and *Trichophyton*) will be prepared and administered according to SOP-JHS-HDC-CL-014 “Delayed type hypersensitivity testing and biopsy procedure”. Beginning at the time of the fourth vaccination, the DTH tests for recall antigens will be repeated. An additional leukapheresis will be required for any patients who have a positive DTH skin test for PEPvIII for immunologic monitoring. The patient will be monitored after the administration of all skin tests for the development of severe allergic reactions. A physician or nurse who has completed an ACLS course will supervise the skin tests, and a cardiac resuscitation cart will be available in the immediate vicinity when performing these procedures. A 5 mm diameter of erythema or induration will be considered positive. Patients with positive reactions at the site of human PEPvIII-KLH will be biopsied under local anesthesia for evaluation of the infiltrate (SOP-JHS-014 “Delayed Type Hypersensitivity Testing and Biopsy Procedure”). The biopsy will be a standard 4 mm “punch” biopsy routinely used in the Dermatology Clinic.

## **5.3 Safety, Toxicity, and Adverse Events**

### **5.3.1 Dose-limiting Toxicity**

DLTs will be tracked using the NCI CTC (Version 3.0) and our own Clinical Neurologic Change (CNC) criteria. CNC will be defined as a decrease in the Mini-mental Status Examination (MMSE) of  $\geq 6$  points, a decrease in KPS of  $\geq 30$  points, or the development of a new focal neurologic deficit. A DLT will be defined as any irreversible CNC, irreversible Grade 3 toxicity, any Grade 4 toxicity, or any life-threatening event not attributable to a concomitant medication, co-morbid event, or disease progression that has been documented histologically. If biopsy cannot be obtained, any new radiographic or clinical changes, as defined above, will be considered a DLT. Also as defined above, any life-threatening event, even if considered a Grade 3 toxicity, will still be considered a DLT even if reversible. CNC and Grade 3 toxicities will be declared irreversible if they cannot be reversed within 2 months of their onset.

### **5.3.2 Management of Toxicities**

Any Grade 4 toxicity or any life-threatening event not attributable to a concomitant medication, co-morbid event, or disease progression, even if reversible, will be considered a DLT. To attribute the Grade 4 toxicity or life-threatening event to tumor progression, tumor progression will need to be confirmed histologically. If biopsy cannot be obtained, any new radiographic or clinical changes that produce a Grade 4 or life-

---

 CNC, Clinical Neurologic Change

 MMSE, Mini-mental Status Examination

threatening toxicity will be considered at DLT. Life-threatening events, as described above, even if considered a Grade 3 toxicity, will still be considered a DLT even if reversible and in such cases no further vaccinations will be given..

If a CNC or Grade 3 NCI CTC toxicity is seen that is not attributable to a concomitant medication, co-morbid event, or disease progression that has been documented radiographically or clinically, the next immunization for that patient will be withheld for up to 2 months or until the NCI CTC toxicity improves to a Grade 2 or until the KPS score returns to within 10 points of baseline or the MMSE returns to within 2 points of baseline. CNC and Grade 3 toxicities will be declared irreversible if they cannot be reversed within 2 months of their onset. If the event cannot be reversed within 2 months of its onset, a DLT will be declared for that patient and no further vaccinations or study-related procedures will be performed. If the event is reversed, but a Grade 3 NCI CTC toxicity or a CNC is again seen with subsequent vaccinations, all further vaccinations and study-related procedures will be withheld and a DLT will be declared. Medical therapy may be used to reverse any toxicity if necessary, but any episode of a CNC requiring surgical intervention will still be considered a DLT even if reversible by surgery.

Patients will be evaluated for toxicity as a whole. If no patients in the first cohort of 3 patients experience a toxicity within 2 weeks another cohort of three patients will be enrolled. If any 2 patients develop a DLT, no further enrollment will be permitted and the study will be closed. Because we have previously safely treated many patients with the vaccine alone, toxicity in each arm will be evaluated independently.

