| Study Design:       | 
Twenty patients with newly-diagnosed EGFRvIII+ high grade glioma (WHO III or IV) will undergo leukapheresis for immunologic monitoring. Only 1 dose level of daclizumab (1 mg/kg) will be assessed. The decision to dose escalate in subsequent trials will be dependent on analysis of the safety and immunologic responses obtained in this trial. Patients will be followed until death. This study will be halted if any 2 patients experience a drug-related Grade IV or irreversible Grade III toxicity. After initial leukapheresis, all patients will then receive RT and concurrent TMZ at a standard targeted dose of 75 mg/m^2/d. Patients with progressive disease during radiation, dependent on steroid supplements above physiologic levels at time of vaccination, unable to tolerate TMZ or whose PBLs fail to meet release criteria will be replaced, but no more than 40 patients will be enrolled overall. Remaining patients will then receive the initial cycle of TMZ at a targeted dose of 100mg/m^2/d for 21 days <math>3 \pm 1</math> weeks after completing RT and will be independently randomized to receive daclizumab versus saline simultaneous with vaccine #1. An additional cohort of 6 patients (cohort #2) will receive serial administrations of daclizumab at vaccine # 1, vaccine # 3, and during the recovery from each TMZ cycle for the first 3 cycles at the same dose. Vaccine #1 will be given on day <math>21 \pm 2</math> days after the start of the 100mg/m^2/d dose of TMZ. While standard dose 21-day TMZ treatment at a target dose of 100 mg/m^2/day is recommended, TMZ regimen may be adjusted at the discretion of the treating neuro-oncologist. Vaccine will always be given on day <math>21 \pm 2</math> of each 28 day TMZ cycle. Vaccines will be given intradermally and divided equally to both inguinal regions. The calculated dosage of daclizumab will be administered in a 50 mL of sterile 0.9% sodium chloride solution via a peripheral or central vein over a 15 minute period. Vaccine #2 and #3 will occur at 2 week intervals. Patients will then be treated monthly with TMZ cycles for a total of 6 cycles after RT. TMZ will be given on days 1-5 of a 28 day cycle. Subsequent vaccines will be given on day <math>21 \pm 2</math> of each of the five remaining TMZ cycles. Cohort # 2 will receive subsequent vaccinations along with daclizumab (1 mg/Kg) on day <math>21 \pm 2</math> for first 3 cycles. Vaccines will then continue monthly until progression. An additional leukapheresis will be required for any patients who have a positive DTH skin test for PEPvIII for immunologic monitoring. Patients will be imaged after vaccine #4 and then bimonthly without receiving any other prescribed antitumor therapy until progression. Blood work for immunologic monitoring will be drawn before vaccine #1 and then each vaccine after vaccine #3. Blood work for sub-clinical autoimmunity will be drawn before vaccine #1 and every 4 months after vaccine #3. As part of standard care for these patients, upon tumor progression, participants may undergo stereotactic biopsy or resection. As this is not a research procedure consent will be obtained separately. However, if tissue is obtained, it will be used to confirm tumor progression histologically and to assess immunologic cell infiltration and EGFRvIII antigen escape at the tumor site.
 |

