| Hispanic or Latino                        | 0                  | 0                    |                     |
| Not Hispanic or Latino                    | 11                 | 9                    | 20                  |

A second cohort of 6 patients (cohort #2) will receive serial administrations of daclizumab at vaccines # 1 and 3 and during the recovery from first 3 TMZ cycles at the same dose. Patients with progressive disease during radiation, dependent on steroid supplements above physiologic levels at time of vaccination, and are unable to tolerate TMZ will be replaced. As a result, 12 patients will be consented but a maximum of 6 patients will receive 3 vaccines and 5 cycles of daclizumab. In cohort #2, patients who do not complete 4 vaccines and 2 doses of daclizumab will be replaced. Based on a predicted accrual rate of 2 patients each month, it is estimated to take 3-6 months to complete this additional cohort. The target distribution for patient enrollment is shown in the following Table:

|           | Patient Numbers | White |        | African-American |        | Hispanic |        | Asian |        | Other |        |
|-----------|-----------------|-------|--------|------------------|--------|----------|--------|-------|--------|-------|--------|
|           |                 | Male  | Female | Male             | Female | Male     | Female | Male  | Female | Male  | Female |
| Cohort #1 | 20              | 10    | 7      | 1                | 1      | 0        | 0      | 0     | 0      | 1     | 0      |
| Cohort #2 | 6               | 3     | 2      | 1                | 0      | 0        | 0      | 0     | 0      | 0     | 0      |
| TOTAL     | 26              | 13    | 9      | 2                | 1      | 0        | 0      | 0     | 0      | 1     | 0      |

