## **10.2 Safety Component**

The study statistician, [name], Ph.D., will be responsible for all statistical analysis. Establishing the safety and efficacy of intradermal immunization with CDX-110 with or without daclizumab will be an important goal of this study and the methods for determining this are outlined above.

Given the lack of significant toxicity in our prior multi-institutional EGFRvIII-targeted immunotherapy trials and those of others in patients with GBM(Yu, Wheeler et al. 2001), and the established safety of the clinically-approved drug daclizumab, and the safety of other clinical approaches to TReg inhibition that have been used recently(Dannull, Su et al. 2005), we believe that it is likely that no significant toxicity will occur. However, any irreversible Grade 3 or reversible Grade 4 toxicity or life-threatening event, prior to tumor progression, will be considered a limiting toxicity. Patients will be randomized to each group in blocks of 3 and patients will be evaluated for toxicity within these groupings. If no patients in a given cohort experience a toxicity within 2 weeks another cohort will be enrolled within that arm. Enrollment will be halted if:

1. Any two patients in a cohort of three experience a DLT; or,
2. Any two patients in a cohort of six consecutively enrolled patients experience a DLT.

Because we have previously safely treated many patients with the vaccine alone, toxicity in each arm will be evaluated independently. We have an existing Data and Safety Monitoring Plan approved by the NCI (See Appendices) for use in these studies.

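### The toxicity halting rule is stated in conflicting forms that give different decisions on the same events, and its trigger and counting unit are not fixed

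*Protocol*

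**What the plan says.** **Halting rule.** The synopsis states, and Protocol 5.1.1 repeats: "This study will be halted if any 2 patients experience a drug-related Grade IV or irreversible Grade III toxicity". There is no window and no restriction to an arm. Section 5.3.2 states: "If any 2 patients develop a DLT, no further enrollment will be permitted and the study will be closed". Section 10.2 halts enrollment on either of two conditions: "Any two patients in a cohort of three experience a DLT; or" "Any two patients in a cohort of six consecutively enrolled patients experience a DLT". The sentence leading into them places the cohorts within an arm: "If no patients in a given cohort experience a toxicity within 2 weeks another cohort will be enrolled within that arm".

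**Counting unit.** One paragraph of 5.3.2 says "Patients will be evaluated for toxicity as a whole" and also "toxicity in each arm will be evaluated independently". Section 10.2 repeats the arm-by-arm statement.

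**Trigger.** Section 5.3.1 makes an irreversible Clinical Neurologic Change (CNC) a DLT. The synopsis and 5.1.1 do not name CNC. Section 10.2 describes its own limiting toxicity (irreversible Grade 3, reversible Grade 4 or life-threatening, before tumor progression), again without CNC, and then writes its two numbered conditions in terms of DLTs.

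**Action.** The study is halted (synopsis, 5.1.1), the study is closed (5.3.2), or enrollment is halted (10.2).

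**Cohort #2.** Section 10.1 adds: "A second cohort of 6 patients (cohort #2) will receive serial administrations of daclizumab at vaccines # 1 and 3". The synopsis and 5.1.1 describe this cohort in the same paragraph as their halting sentence. Sections 5.3.2 and 10.2 do not say how it is counted.

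**The concern.** A stopping rule has to give one answer when events occur. Here the answer depends on which section is opened. Section 9.3 makes the principal investigator responsible for seeing that stopping rules are met, but does not say which rule applies. If the choice is made after DLTs have been seen and their arms are known, the rule is no longer prespecified. This matters for patients because section 3.6 acknowledges that blocking the IL-2 receptor may unleash harmful autoimmunity and asks for particular attention to it. The trigger matters as well, because neurologic decline alongside progression is to be expected in high-grade glioma. Whether such a decline counts toward a limit of two can decide whether the trial continues.

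**Working it through.** The Protocol gives no acceptable DLT rate and no halting probability, so there is no figure to reproduce. The check has four steps.

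**1. Same events, different decisions**

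| Events | 5.3.2, pooled | 5.3.2, by arm | 10.2 |
|---|---|---|---|
| DLTs in patients 1 and 7 of one arm | close | close | not met |
| One DLT in each arm | close | continue | not met |
| DLTs in patients 1 and 5 of one arm | close | close | halt enrollment |

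**2. How often two DLTs in one arm escape 10.2 (no risk assumption)**

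With 10 patients per arm (8.1.1), two DLTs can fall in 10×9/2 = 45 position pairs. All 45 meet the any-two rule.
- Sliding six: pairs six or more places apart escape, 4+3+2+1 = 10 of 45 (22%).
- Successive cohorts of three giving sixes 1–6, 4–9 and 7–10: 3×4 + 3×1 = 15 of 45 escape (33%).
- Separate blocks 1–6 and 7–10: 6×4 = 24 of 45 escape (53%).

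These counts weight all pairs equally and take exactly two DLTs at full accrual.

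**3. Halting probability**

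The DLT risk p is an assumption: 5%, 10% or 20%. Events are independent, each arm accrues 10, and q = 1−p.
- Any two of n: A(n) = 1 − qⁿ − n·p·qⁿ⁻¹.
- Section 10.2 with a sliding six in an arm of 10: S = 1 − q¹⁰ − 10pq⁹ − 10p²q⁸. The last term is the 10 escaping pairs; three DLTs cannot all be six apart in ten places. Two of three is contained in two of six.
- Either of two arms with equal risk: 1 − (1−x)².

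At p = 0.10, q¹⁰ = 0.3487, 10pq⁹ = 0.3874 and 10p²q⁸ = 0.0430. So A(10) = 0.264 and S = 0.221. In either arm these become 1 − 0.7361² = 0.458 and 1 − 0.7791² = 0.393. Pooled, A(20) = 0.608.

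| Assumed risk | Rule | 5% | 10% | 20% |
|---|---|---|---|---|
| Daclizumab arm only | any two (pooled or by arm) | 0.09 | 0.26 | 0.62 |
| | 10.2, sliding six | 0.07 | 0.22 | 0.56 |
| Equal in both arms | any two, pooled | 0.26 | 0.61 | 0.93 |
| | any two, by arm | 0.16 | 0.46 | 0.86 |
| | 10.2, sliding six, either arm | 0.13 | 0.39 | 0.80 |

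With separate blocks of six, 10.2 falls to 0.05/0.16/0.46 (one arm) and 0.09/0.30/0.71 (either arm), so each gap widens.

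**4. Attribution to progression**

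Take an irreversible CNC with progression on MRI and no biopsy. Section 5.3.1 excuses progression that is documented histologically, and says that without a biopsy new radiographic or clinical changes count as a DLT. The second paragraph of 5.3.2, which governs CNC and Grade 3 events, accepts radiographic or clinical documentation. That paragraph is the one that leads to declaring a DLT if the event does not reverse within two months. The event is therefore a DLT under the natural reading of 5.3.1 and is excused under 5.3.2.

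**The case against.** The strongest reply is that each sentence is a sufficient condition. None says that enrollment stops only then, and 10.2 never tells the team to continue after two DLTs. Obeying every sentence would mean applying the strictest, pooled any-two rule. It is true that a reader might infer that 10.2 licenses continuation, and the text does not say that. But the Protocol nowhere says the strictest rule prevails, and both 5.3.2 and 10.2 say the arms are judged independently, which points away from pooling. The ambiguity remains.

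Four further inferences would go too far.
- The any-two-DLT rule is not stated throughout. It appears in 5.3.2 only; the synopsis and 5.1.1 use a narrower, drug-related trigger.
- Section 7.3 does not add to the attribution conflict. Its DLT sentence applies where radiographic or histologic evidence of progression is absent, so it does not cover the MRI case.
- Cohort #2 is not unaddressed everywhere. On a plain reading of the synopsis and 5.1.1 its patients count; 5.3.2 and 10.2 leave it open.
- Attribution is a tension, not a flat contradiction. If the histology clause in 5.3.1 attaches only to life-threatening events, 5.3.2 could be read as completing it. The no-biopsy sentence in 5.3.1, which refers back to the changes defined above it, makes that reading harder.

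Section 9.3 also provides an audit after three subjects, twice-yearly review and the possibility of closure. These soften the practical risk but do not say which rule to apply.

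**Conclusion.** The concern holds for the halting rule and its counting unit. The sections give different decisions on identical events, and that does not depend on any assumed risk. The trigger mismatch holds for CNC, and for the separate progression test in 10.2. Attribution is a drafting tension between 5.3.1 and 5.3.2.

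The numerical effect is modest or large depending on assumptions the Protocol does not settle. If only daclizumab carries risk, the gap between any-two and 10.2 is 0.02/0.04/0.07 at 5/10/20% risk. This is the case closest to 9.2.12, which reports no toxicities in 40 patients given the vaccine. With equal risk in both arms, the gap is 0.13/0.22/0.13 if counting is pooled and 0.03/0.07/0.05 if it is by arm. A reader might take the pooled equal-risk gap as the expected effect; it requires the saline arm to carry the same DLT risk, which the Protocol does not suggest. The case for correction rests on conflicting safety rules, not on a large gap.

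**What to change.** 1. Replace the two numbered conditions in 10.2 with the any-two-DLT rule of 5.3.2, and state one action (study closed, or enrollment halted) throughout.
2. Use the 5.3.1 DLT definition, including irreversible CNC, as the trigger in the synopsis, 5.1.1, 5.3.2 and 10.2, and remove the separate limiting-toxicity sentence from 10.2.
3. Keep either pooled or arm-by-arm evaluation in 5.3.2 and 10.2, and delete the other. State that cohort #2 counts in the daclizumab total, or in the study total if counting is pooled.
4. Align 5.3.1 with 5.3.2. For example, require histology for Grade 4 or life-threatening events and accept radiographic or clinical documentation for CNC and Grade 3 events. The reverse is possible, provided both sections say the same.

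The cost is amendment wording, with no new visits or data. The downside is that early closure becomes more likely than under 10.2. At 5% risk it rises from 0.07 to 0.09 if only the randomized daclizumab arm carries risk. If both arms do, it rises from 0.13 to 0.16 by arm or 0.26 pooled. Counting cohort #2 adds to this: any two of 16 daclizumab patients at 5% gives 1 − 0.95¹⁶ − 16×0.05×0.95¹⁵ = 0.19, and any two of 26 pooled gives 0.38 if all carry that risk. The clinical team should choose the counting unit with these figures in view.
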